### Outcomes and Measurements

The primary and secondary outcome measures will be changes in cycloplegic autorefraction in spherical equivalent refraction and axial length, respectively, measured every 6 months over 2 years from baseline. Other outcomes include peripheral refraction, pupil size, choroidal thickness, amplitude of accommodation, accommodative lag, corneal curvature, noncontact intraocular pressure, visual performance questionnaire, and treatment compliance (assessed via the frequency and/or duration of the use of atropine and bright light therapy).

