### Statistical Analyses

The latest version of the SPSS software (IBM Corp) will be used for statistical analyses. This study will use the same statistical approach as that used in the previous phase 1 study [15]. Data from the right eyes will be used for analyses. The normality of the data will be examined using the Kolmogorov-Smirnov test. Demographic and optometric data will be presented as means and SDs or as numbers and percentages as appropriate. The chi-square test (or, if appropriate, the Fisher exact test) and one-way ANOVA will be performed to compare baseline between-group differences in demographics (age and sex). Changes in primary, secondary, and other outcomes at different time points will be analyzed using a mixed-effects model for repeated measures, which includes fixed effects for the treatment group, time, the interaction between group and time, and covariates including age and baseline myopia. If statistically significant differences in baseline demographic characteristics between arms are found, these will also be adjusted for.

The progression of myopia over 2 years will be calculated as the difference in cycloplegic autorefraction in spherical equivalent refraction and axial length between the baseline and the 2-year visit. The relative treatment effect in each arm will be determined by dividing the difference in myopia progression between the treatment group and the control group in the phase 1 study [15] by myopia progression in the control group and then multiplying by 100%. Additionally, the absolute treatment effect [29] will be presented to facilitate comparison with other studies. Multiple regression analysis will be used to identify factors associated with myopia control effectiveness.

All analyses will follow the intention-to-treat approach. Missing values of outcome variables and covariates will be replaced using a multiple imputation procedure with 10 sets of imputations assuming missingness at random. Sensitivity analyses for the primary outcomes include (1) complete-case analysis and (2) per-protocol analysis. All analyses will be 2-tailed, with a significance level of 5%.

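### A baseline significance test decides whether sex enters the primary model; pre-specify sex instead, and name each outcome's own baseline where one is measured

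*Protocol article*

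**What the plan says.** All of this is in the protocol article; no statistical analysis plan is shown.

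- **Model.** Statistical Analyses puts every outcome under one approach: "Changes in primary, secondary, and other outcomes at different time points will be analyzed using a mixed-effects model for repeated measures". The fixed effects are group, time, "the interaction between group and time, and covariates including age and baseline myopia".
- **Baseline tests.** The chi-square (or Fisher) test and one-way ANOVA are used "to compare baseline between-group differences in demographics (age and sex").
- **Rule.** "If statistically significant differences in baseline demographic characteristics between arms are found, these will also be adjusted for".
- **Outcomes.** Outcomes and Measurements defines the primary and secondary outcomes as "changes in cycloplegic autorefraction in spherical equivalent refraction and axial length, respectively, measured every 6 months over 2 years from baseline". It then continues: "Other outcomes include peripheral refraction, pupil size, choroidal thickness, amplitude of accommodation, accommodative lag, corneal curvature, noncontact intraocular pressure", followed by the visual performance questionnaire and compliance.
- **Meaning of baseline myopia.** Inclusion Criteria expresses myopia as spherical equivalent, so baseline myopia is the primary outcome's own baseline.
- **Allocation.** Randomization and Masking gives 1:1 simple randomisation stratified by two age groups. Sex is not a stratification factor.

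**The concern.** If randomisation is done properly, any baseline difference between the arms is due to chance. A p-value for that difference tests a null hypothesis already known to be true. It does not show whether the variable predicts myopia progression, which is what decides whether adjustment is worthwhile. A rule built on that p-value has two consequences:

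1. The primary model is unknown until the arms have been compared at baseline, so it is not fixed in advance.
2. The rule leaves sex out in roughly 19 trials of 20, so any prognostic value of sex goes almost unused.

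A smaller point concerns the outcomes other than SER. The covariates named for all of them are age and baseline myopia. For axial length, pupil size, intraocular pressure, accommodation and choroidal thickness, baseline myopia is not the outcome's own baseline. If no own-baseline term is added, variation in the change score that the baseline value predicts stays in the error term.

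**Working it through.** **Inputs from Sample Size Calculation and Statistical Analyses.** Difference 0.25 D over 2 years; two-sided 5%; power 85%; 56 evaluable per arm. SD 0.44 D, reading the printed spread around -0.64 D as plus or minus 0.44.

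**Inputs assumed, because the document gives none.** The correlation of sex with the 2-year change, and the baseline-to-follow-up correlation r of the other outcomes.

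**Step 1: reproduce the plan's figure.** n = 2 × (1.960 + 1.036)² × 0.44² / 0.25² = 55.6, so 56 per arm. Normal-approximation power at 56 is 0.852. The stated figure reproduces.

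**Step 2: which variable the rule touches.** The named demographics are age and sex. Age is in the model whatever the test shows. That leaves sex.

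**Step 3: how the rule behaves.** Simulation of 20,000 trials per scenario, with 56 per arm, sex split 50/50, total SD 0.44 and a single 2-year change. Sex was adjusted for never, always, or only if the uncorrected chi-square test gave p < 0.05. The test was significant in 4.4-4.9% of trials.

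| Assumed correlation of sex with outcome | Type I error, rule | Type I error, always | Power for 0.25 D, never | Power, rule | Power, always |
|---|---|---|---|---|---|
| 0.1 | 0.050 | 0.050 | 0.847 | 0.847 | 0.847 |
| 0.3 | 0.050 | 0.052 | 0.847 | 0.850 | 0.876 |
| 0.5 | 0.044 | 0.049 | 0.844 | 0.853 | 0.930 |

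The rule performs almost like never adjusting.

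**Step 4: the same in dioptres.** With an even sex split, a sex difference d corresponds to a correlation of d × 0.5 / 0.44. For an assumed d = 0.2 D this is 0.227. Variance explained is 0.227² = 0.052, and the residual SD is 0.44 × √(1 - 0.052) = 0.428 D. Power with sex always in the model is then about 0.865, against about 0.85 under the rule. For d = 0.1 D and 0.3 D (correlations 0.11 and 0.34), power with sex always in the model is about 0.85 and 0.89.

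**Step 5: own-baseline adjustment.** With equal variances at baseline and follow-up, scaled to 1, a change score has variance 2(1 - r). Adjusting for its own baseline leaves 1 - r². The ratio is (1 - r²) / [2(1 - r)] = (1 + r)/2.

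| Assumed r | Variance ratio | Reduction |
|---|---|---|
| 0.5 | 0.75 | 25% |
| 0.7 | 0.85 | 15% |
| 0.9 | 0.95 | 5% |
| 0.95 (plausible for axial length) | 0.975 | 2.5% |

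The comparison is with an unadjusted change score. The planned model already holds age and baseline myopia, so the net gain may be smaller.

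**The case against.** The case for leaving the plan alone has real force.

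- **The two covariates most clearly called for are already fixed.** Age and baseline myopia enter regardless of any test, and age group is also a stratification factor. Only sex is conditional. This stands, and it limits the point to one variable.
- **The gain may be nil.** At a correlation of 0.1 there is no difference in power. This stands. Adjusting is still nearly free, because one pre-specified covariate costs one degree of freedom.
- **The own-baseline remark reads an open list as closed.** The wording is "covariates including age and baseline myopia", which excludes nothing, and a full protocol or analysis plan not shown may name the rest. This stands, so that part is a request for clarification. The conditional rule for demographics is different: it is a stated rule, not an omission.

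Three stronger readings are tempting, and the document supports none of them.

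- **That every outcome is adjusted for something other than its own baseline.** For the primary outcome this is false, because baseline myopia is baseline SER.
- **That the primary analysis switches model at random or loses error control.** The test fires in about 5% of trials, and type I error under the rule is 0.044-0.050.
- **That the rule biases the estimate.** Take 39/67 girls in one arm and 28/67 in the other: uncorrected chi-square p = 0.057, so sex stays out. The imbalance is 11/67 = 16.4 percentage points. With an assumed sex difference of 0.2 D (range 0.1-0.3 D), the estimate shifts by 0.164 × 0.2 = 0.033 D (0.016-0.049 D), or 13% of 0.25 D. But the split was chosen to fall just above 0.05. The shift is a chance deviation in one trial, about 0.4 of a standard error (0.44 × √(2/56) = 0.083 D). Averaged over randomisations it is zero.

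**Conclusion.** The point holds in a limited form. The plan lets a baseline significance test choose a covariate of the primary model, and among the variables it names that covariate is sex. The cost is a primary model not fixed in advance, plus lost precision. Power is lower than with sex always in the model by about 0.015 at an assumed 0.2 D sex difference and by about 0.026 at an assumed correlation of 0.3; at 0.1 nothing is lost. Neither the validity of the test nor the average estimate is at risk.

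These figures rest on SD 0.44 D, 56 evaluable children per arm, an even sex split and a single 2-year change in place of the full repeated-measures model. The prognostic strength of sex is assumed throughout.

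The own-baseline remark is secondary. It matters little for axial length, the only named secondary outcome. For less stable measures the gain could be moderate, at correlations that the document does not supply. It does not apply to outcomes without a baseline value: the visual performance questionnaire is first given at 6 months, and Table 1 shows no baseline assessment of visual performance or compliance.

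**What to change.** 1. Delete the sentence that makes adjustment depend on baseline significance. Report baseline characteristics descriptively, and do not use baseline tests to choose covariates.
2. State a closed covariate list for the primary model: age, sex and baseline SER.
3. As a minor addition, for axial length and the other outcomes measured at baseline (such as pupil size, intraocular pressure, accommodation and choroidal thickness), name the outcome's own baseline as a covariate alongside baseline myopia. Exempt outcomes with no baseline value, such as the visual performance questionnaire and compliance.
4. If a full protocol or analysis plan already lists the covariates, bring the two texts into line.

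The cost is wording only. The baseline measures needed are already in the visit schedule, and sex is already among the baseline demographics. The change should be dated before the final data are analysed; the article expects data collection to end in April 2026.

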**Conclusions:**

This study will provide new information on whether the combination of bright light therapy and low-dose atropine is more effective than atropine alone in slowing down myopia progression. It will also assess the effectiveness of low-dose atropine used twice daily. Combining bright light therapy and atropine could become a new treatment option if shown to be effective. New data on the effectiveness of using atropine twice daily might also expand available treatment options.

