As no current treatment has been found to be able to completely halt myopia progression, another option is the potential use of a combination treatment. It is hypothesized that bright light therapy could provide additive efficacy to slow myopia progression when used in combination with low-dose atropine. Low-dose atropine has demonstrated a dose-dependent effect on slowing myopia with minimal side effects [16]. This combination is promising as there are preliminary data suggesting that these 2 therapies work on different mechanisms. While the exact mechanism for atropine’s action is still unknown, it is thought to affect the development of myopia mainly by acting as a reversible competitive antagonist of acetylcholine muscarinic receptors that are found in many parts of the eye [17]. Regarding bright light therapy, its inhibitory effect on myopia is suggested to be mediated by the retinal dopaminergic pathways [18].

On the basis of these rationales, this clinical trial was designed to examine the combined effect of bright light therapy and low-dose atropine on myopic progression. The primary aim of this trial is to investigate whether the combination treatment with bright light therapy and low-dose atropine would be more effective than atropine alone. This trial will also assess the effectiveness of low-dose atropine in slowing myopia progression. Factors associated with the effectiveness of the treatments will also be identified. In addition, compliance and participant acceptability (particularly in terms of visual performance) of the combination therapy will be evaluated.

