## Methods

### Study Design and Setting

This protocol describes a single-site, 2-arm, single-masked (examiner-masked) randomized controlled trial comparing the effectiveness of low-dose atropine alone and in combination with bright light therapy in retarding myopia progression. This manuscript is based on protocol version 1.6 (September 2022). This study will last for 2 years and is an auxiliary study to a previous study (phase 1 study) [15] conducted by the same team sharing the same study design except for the choice of treatment. The phase 1 study [15] will consist of 1 control group and 2 treatment groups, whereas this phase 2 study will consist of 2 treatment groups only. This paper will only describe the design of the phase 2 study, and details of the intervention for each group are shown in Figure 1 [15]. The investigation will be separated into 2 phases due to logistical issues. Participants from the phase 1 study will not continue into the phase 2 study. This study consists of 2 arms: atropine and atropine combined with bright light therapy. Participants will be randomized to the 2 treatment groups at a ratio of 1:1 using an age-stratified simple randomization. Data from the 2 phase 2 treatment groups will be compared with each other, and comparisons with phase 1 data will be conducted for exploratory analysis. Identical inclusion criteria will be used for both studies to minimize potential selection bias. The application of consistent methodologies and statistical approaches will enable meaningful comparisons across interventions.

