A recent 1-year–long randomized clinical trial by He et al [41] provides supporting evidence for this hypothesis. In their study, the axial elongation and spherical equivalent refraction progression in the twice-daily group (n=36) were 34% and 53% lower, respectively, than in the once-daily group (n=34). There were no clinically significant differences between the 2 groups in safety parameters, including accommodation amplitude, pupil diameter, and intraocular pressure. The study proposed in this paper, with a larger sample size and longer follow-up, will provide additional insights into optimizing the balance between efficacy and safety in low-dose atropine treatment for myopia control.

The strengths of this study include its prospective, randomized design and the use of masked examiners. The primary limitation of this study is the lack of masking of participants. The study duration is only 24 months due to budget constraints, so longer-term results will not be available. In addition, while the effectiveness of bright light therapy is examined in this study, further research is still needed to determine the optimal light level. Whether the benefit, if any, would apply to patients with different characteristics also remains to be assessed.

The results of this study will be disseminated at scientific conferences and in peer-reviewed, indexed journals in the fields of optometry and ophthalmology.

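### The percentage treatment effect, and the aim of assessing atropine, rest on a non-randomised phase 1 control group, with no adjustment or interval attached to the ratio

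*Protocol article*

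**What the plan says.** Study Design and Setting describes two arms, both on atropine, randomised 1:1 against each other. Phase 1 was a separate study with different children and included a control group. The same section says that "comparisons with phase 1 data will be conducted for exploratory analysis" and cites the same eligibility criteria and consistent methods in support.

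Statistical Analyses analyses the outcomes with a mixed-effects model for repeated measures containing group, time, their interaction, and "covariates including age and baseline myopia". The next paragraph takes progression as the difference "between the baseline and the 2-year visit". The relative effect in each arm comes from "dividing the difference in myopia progression between the treatment group and the control group in the phase 1 study" "by myopia progression in the control group and then multiplying by 100" percent. An absolute effect is also to be presented. No covariates or interval are named for the ratio, and the exploratory label is not repeated there.

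On aims, the Introduction says: "This trial will also assess the effectiveness of low-dose atropine in slowing myopia progression". The Abstract's Conclusions say: "It will also assess the effectiveness of low-dose atropine used twice daily". The limitations in the Discussion cover unmasked participants, the 24-month duration, the optimal light level and applicability to other patients. They do not mention the external comparator.

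**The concern.** With every child in this trial on atropine, nothing inside it shows how the same children would have progressed untreated. The only comparator that the article offers for atropine's effectiveness is the phase 1 control group. Any difference between the two cohorts in age mix, baseline myopia, type of volunteer, calendar period or season goes straight into the percentage, where it looks like drug effect. The denominator is also an estimate, so a bare percentage hides part of its own uncertainty.

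The percentage is the figure most likely to be quoted and set beside other myopia trials. A reader who meets it under the name of treatment effect, in a report of a randomised trial, may take it for a randomised result.

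**Working it through.** **1. Which comparison supports which claim**

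| Claim | Comparator | Randomised? |
|---|---|---|
| Combination vs atropine (primary aim) | Atropine arm, same trial | Yes |
| Relative effect in each arm | Phase 1 control group | No |
| Effectiveness of low-dose atropine | Only phase 1 control available | No |
| Twice-daily vs once-daily atropine | No comparator described | Not tested |

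**2. The plan's own figure**

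The article gives no figure for the phase 1 comparison. Its sample size covers the randomised comparison only. Inputs from Sample Size Calculation: difference 0.25 D, SD read as 0.44 D, two-sided 5%, power 85%.

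n = 2 × (1.960 + 1.036)² × 0.44² / 0.25² = 2 × 8.978 × 3.098 = 55.6, so 56 per group. This reproduces the stated 56 and supports reading 0.44 D as the SD.

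**3. Sensitivity of the percentage to the control group**

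Write T for progression on treatment and C for progression in the phase 1 control group, both as positive dioptres. Relative effect = 100 × (C − T) / C.

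T = 0.64 D comes from Sample Size Calculation (the cited 0.01% atropine group). C is not in the document and is assumed:

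- C = 0.8: 100 × 0.16 / 0.8 = 20.0%
- C = 1.0: 100 × 0.36 / 1.0 = 36.0%
- C = 1.2: 100 × 0.56 / 1.2 = 46.7%

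Suppose comparable untreated children would have progressed 1.0 D, but the phase 1 controls differed by 0.2 D for reasons unrelated to treatment. The reported percentage moves by 20.0 − 36.0 = −16 points or 46.7 − 36.0 = +10.7 points. The 0.2 D is also an assumption.

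**4. Sampling error of the ratio**

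Assume SD 0.44 D and 54 children in both groups (67 × 0.80 = 53.6 for a phase 2 arm; the phase 1 SD and size are not given). By the delta method, with r = T / C:

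- standard error of each mean = 0.44 / √54 = 0.0599 D
- SE(r) = (0.0599 / C) × √(1 + r²)
- at C = 1.0: 0.0599 × √(1 + 0.64²) = 0.0711
- 95% half-width = 1.96 × 0.0711 = 0.139, about ±14 points, before any cohort bias.

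**5. If the phase 1 difference were tested at 5%**

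With 56 per group and SD 0.44 D in both, the standard error of the difference is 0.44 × √(2/56) = 0.083 D. With no drug effect at all, a pure cohort shift of 0.10 D would give p < 0.05 in about 23% of trials, and a shift of 0.20 D in about 67%.

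**The case against.** The strongest reply is that Study Design and Setting already classes every comparison with phase 1 as exploratory. The relative effect is such a comparison, so the label covers it without being repeated. This stands: a reader might infer that the plan contradicts itself on the status of the comparison, and it does not. What remains is that the aim, as worded in the Introduction and the Abstract, and the list of limitations give the reader no such warning.

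A reader might also infer that the trial has put its randomised contrast aside. The documents do not support that. The mixed model estimates combination vs atropine, the Introduction names it as the primary aim, and the sample size is built on it. No primary inference depends on phase 1.

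Third, the formula need not be unadjusted. Progression is written as a simple change and no covariate is tied to the ratio, but model-adjusted means are not excluded, and the article refers to the phase 1 statistical approach, which is not shown. The fair statement is that the ratio as written carries no adjustment, not that adjustment is ruled out.

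Fourth, the shared eligibility criteria are a real safeguard. They fix the eligible range (7 to 12 years, −0.75 to −5.00 D), but not the mix of children within it or the calendar period.

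Finally, the article does not claim to test twice-daily against once-daily dosing within this trial. The Discussion's statement that the study "will provide additional insights into optimizing the balance between efficacy and safety in low-dose atropine treatment" is soft wording and should not be read as such a claim. It does follow a description of a trial that made that comparison, which is a reason to say plainly that this one does not.

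**Conclusion.** The point holds as a should-fix. The percentage effect in each arm, and any conclusion on atropine's effectiveness, rest on a control group that was not randomised against these arms. The formula as written does nothing to reduce or display the resulting uncertainty. The primary comparison, its model and its sample size are untouched.

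The size is illustrative. With 0.64 D on treatment and control progression near 1.0 D, a 0.2 D cohort difference moves the percentage by −16 or +10.7 points, and sampling error is about ±14 points. The control progression, the cohort difference, and the phase 1 SD and group size are assumptions. The documents do not show that a cohort difference exists. They show that the ratio would pass one on in full if it did.

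**What to change.** 1. **Statistical Analyses, phase 1 comparison.** Estimate it from one model on data from both phases, adjusted for at least age and baseline myopia. Report the difference and the percentage with a 95% CI, by bootstrap or Fieller's method, so that the interval reflects the estimated denominator. Label both as exploratory and non-randomised. Adjustment cannot remove unmeasured differences or a period effect that coincides with phase, so the label is needed even after adjustment.
2. **Statistical Analyses, treatment effect.** Report the randomised between-arm difference, in D for refraction and mm for axial length, with 95% CI, as the trial's treatment effect.
3. **Introduction, and Conclusions of the Abstract.** Say that atropine's effectiveness is assessed only through an exploratory external-control comparison, and that twice-daily vs once-daily dosing is not tested. Add the same to the limitations in the Discussion.

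The cost is wording, one extra model, and weaker claims about atropine. The model needs individual phase 1 data; the article says that the same team runs that study. The change should be settled before the 2-year results are analysed. Data collection was expected to finish in April 2026.

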### Sample Size Calculation

The sample size is estimated based on the 2-year change in refractive error in the 0.01% atropine treatment group (−0.64, –0.44 to +0.44 D) from a previous myopia control study [20]. Assuming that, over 2 years, combination treatment is more effective than 0.01% atropine alone by 0.25 D, which is considered a clinically significant change, 56 participants per group will be required. This sample size will enable the demonstration of a statistically significant difference between the 2 groups at a 5% significance level with 85% power. The sample size for each study arm will be adjusted to 67 per arm assuming a 20% loss to follow-up. As a result, a total sample size of 134 participants will be recruited for this study.

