### Randomization and Masking

Participants will be randomized to the 2 treatment groups at a ratio of 1:1 using stratified simple randomization. The randomization list will be generated using a random number generator in a Microsoft Excel spreadsheet. Participants will be stratified into 2 age groups (7-9 years and 10-12 years). This is a single-masked study in which examiners are masked to the treatment allocation. Allocation concealment will be ensured using sequentially numbered, opaque, sealed envelopes. The envelopes will be opened by the designated unmasked investigators in numerical order only after the participants are enrolled. To maintain masking, access to the randomization list will be limited to the trial steering committee; study management committee; statistician; and unmasked investigators designated to handle randomization, allocation, and delivery of group assignments. These individuals will not be involved in participant enrollment or data collection.

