### Procedures

Mass emails to the staff of Hong Kong Polytechnic University, advertising posts on social media (Facebook and Instagram), and referrals from parents or guardians who are already participating in the study will be used to recruit participants. Parents or guardians and their children will be invited to the Optometry Research Clinic for a screening visit to confirm their eligibility. Informed consent and assent will be obtained upon confirmation of fulfillment of the inclusion criteria.

Successfully enrolled participants will be randomly allocated to 1 of the 2 arms after baseline measurement. Delivery of spectacles and a light therapy lamp will be arranged 2 weeks after the baseline visit. Training will be provided to participants and parents or guardians on how to set up and use the light therapy lamp at home. The participants in both treatment groups will be asked to return 1 month after the intervention for aftercare appointments to ensure that there are no allergic reactions to atropine or adverse events associated with the light therapy lamp. Participants will also be asked to return for regular follow-up visits with the study ophthalmologist for dispensing of 0.01% atropine.

Data collection will be conducted every 6 months from the baseline visit up to 24 months. Baseline measurements will include demographic data; medical and medication history; visual acuity; tests for strabismus, autorefraction, and keratometry; pupil size; amplitude of accommodation; accommodative lag; subjective and objective refraction with and without cycloplegia; intraocular pressure; choroidal thickness; external and internal ocular health; peripheral refraction; and axial length via the IOLMaster 500 (ZEISS) and other ocular biometry (eg, corneal curvature, corneal thickness, anterior chamber depth, and lens thickness) via the Lenstar LS 900 (Haag-Streit AG). In addition, questionnaires on visual performance, daily activities, and compliance will be administered at the 6-, 12-, 18-, and 24-month visits. A SPIRIT schedule of the study is shown in Table 1.

**Table 1. T1:** Schedule of enrollment, interventions, and assessments.

Timepoint	Baseline	1 month	6 months	12 months	18 months	24 months
Enrollment						
Allocation	✓					
Interventions						
Single treatment: atropine & single vision lenses		✓	✓	✓	✓	✓
Combination treatment: bright light therapy & atropine & single vision lenses		✓	✓	✓	✓	✓
Assessments						

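### Ten imputations with 20% planned loss leave avoidable simulation noise in a borderline p-value; raising the number to 100 is a cheap, minor improvement

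*Protocol article*

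**What the plan says.** The Statistical Analyses section analyses outcomes over time with a mixed-effects model for repeated measures. Its fixed effects are group, time and their interaction, with age and baseline myopia among the covariates. Analyses follow intention to treat, and missing data are handled as follows: "Missing values of outcome variables and covariates will be replaced using a multiple imputation procedure with 10 sets of imputations assuming missingness at random". Tests are two-sided at 5%. The sensitivity analyses named for the primary outcome are complete-case and per-protocol.

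The expected amount of missing data appears under Sample Size Calculation: "The sample size for each study arm will be adjusted to 67 per arm assuming a 20% loss to follow-up". Under Procedures, the visits are six-monthly: "Data collection will be conducted every 6 months from the baseline visit up to 24 months".

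**The concern.** Multiple imputation draws random values, so the pooled estimate, standard error, degrees of freedom and p-value all vary from run to run. The variation shrinks as the number of imputations, m, grows. Ten is ample for a stable point estimate. It is less ample for a stable p-value when a noticeable share of the information is missing and the result is judged against a fixed 5% threshold.

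What is at stake is reproducibility. If the primary result is borderline, part of the reported p-value reflects the random draw and not the children's data. That part can be made small at almost no cost. The objection is to a number the article states, not to a detail it leaves out.

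**Working it through.** **Inputs from the protocol article.** m = 10, two-sided 5% (Statistical Analyses). Difference 0.25 D, 85% power, 20% loss, 67 per arm (Sample Size Calculation). Allocation 1:1 (Randomization and Masking). Visits at 6, 12, 18 and 24 months (Procedures). The SD is read as 0.44 D from the spread printed beside the mean of −0.64 D.

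**Assumed, because the documents do not give them.** A fraction of missing information (FMI) of 0.1-0.2, with 0.05 and 0.30 as outer values, and a correlation between visits of 0.5-0.9.

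**Step 1: reproduce the plan's figure.** n = 2 × (1.960 + 1.036)² × 0.44² / 0.25² = 55.6, so 56 per group, as stated. The 67 per arm is 56 × 1.2 = 67.2. The reading of the SD is therefore consistent with the plan.

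**Step 2: efficiency and noise.** Relative efficiency = 1/(1 + FMI/m). Monte Carlo SD of the estimate, in units of its standard error, = √(FMI/m). At FMI 0.20 and m = 10 this is √0.02 = 0.141. A limiting z of 1.96 (p = 0.05 with unlimited imputations) is then reported within 1.96 ± 1.96 × 0.141, that is 1.68 to 2.24, or p from 0.092 down to 0.025.

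| FMI | m | Efficiency | Noise SD / SE | 95% range of reported p when limiting p = 0.05 |
|---|---|---|---|---|
| 0.10 | 10 | 99.0% | 0.100 | 0.031-0.078 |
| 0.10 | 50 | 99.8% | 0.045 | 0.041-0.061 |
| 0.10 | 100 | 99.9% | 0.032 | 0.043-0.058 |
| 0.20 | 10 | 98.0% | 0.141 | 0.025-0.092 |
| 0.20 | 50 | 99.6% | 0.063 | 0.037-0.066 |
| 0.20 | 100 | 99.8% | 0.045 | 0.041-0.061 |

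At m = 10 the outer values give 0.036-0.069 (FMI 0.05) and 0.021-0.105 (FMI 0.30).

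**Step 3: how often two runs disagree at 5%, over all trials.** The same normal approximation, simulated, gives:

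| FMI | m | 85% power | No effect |
|---|---|---|---|
| 0.10 | 10 | 2.6% | 1.3% |
| 0.10 | 50 | 1.2% | 0.6% |
| 0.10 | 100 | 0.8% | 0.4% |
| 0.20 | 10 | 3.7% | 1.9% |
| 0.20 | 50 | 1.7% | 0.8% |
| 0.20 | 100 | 1.2% | 0.6% |

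**Step 4: full simulation.** The approximation ignores noise in the standard error and degrees of freedom, so whole trials were also simulated. They had 67 per arm, a 0.25 D effect, four visits, 20% monotone dropout, sequential regression imputation and Rubin pooling. As a simplification, the analysis was an unadjusted comparison at 24 months. The estimated FMI was 0.12 to 0.20 for correlations from 0.9 down to 0.5. At m = 10, two runs disagreed in 5.6-7.2% of 250 trials per setting. At m = 50 they disagreed in 0-1% of 80 trials. The sampling error is material: √(0.056 × 0.944/250) = 1.5 percentage points, so 5.6% carries a margin of about ±2.9 points and does not conflict with step 3. A second simulation (correlation 0.7-0.9, FMI about 0.11-0.17) gave 3-8% at m = 10 and 1-2% at m = 100.

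Taken together, two runs disagree in about 2-8% of trials at m = 10, a little less where there is no effect and FMI is low, and in about 1-2% or less at m = 100.

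**The case against.** The strongest defence is that nothing here is wrong. Rubin's variance includes a term for finite m, and its degrees of freedom adjust for it. Ten imputations therefore cause no bias, and no inflation of the type I error has been shown. This stands in full, as does the loss of only 1-2% in efficiency.

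Four stronger readings are tempting, and the documents do not support them.

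- **A rerun would readily reverse the trial's conclusion.** Among simulated data sets chosen to have p between 0.035 and 0.065, 24-36% of reruns at m = 10 crossed 0.05. That rests on six data sets per correlation and on a selected band. With the expected z of 1.960 + 1.036 = 2.996, the band runs from z = 1.845 to 2.108 and holds Φ(−0.888) − Φ(−1.151) = 0.187 − 0.125, about 6% of trials. Crossing there concerns 0.24 × 6% to 0.36 × 6%, about 1.4-2.2% of all trials, plus some from just outside the band.
- **20% of the information is missing.** The 20% is a planning rate for loss to follow-up. Earlier six-monthly visits inform the 24-month value, so the FMI is probably at or below 0.20.
- **The seed is left uncontrolled.** A fixed seed would remove any choice among runs even at m = 10. Its absence from a condensed article, with the analysis plan not shown, is no finding.
- **Imputation is unnecessary because the mixed model already handles missing outcomes.** A repeated-measures likelihood does use all observed outcomes under missing at random without random draws. The plan, however, also imputes covariates, which that model does not handle by itself. It can therefore serve as a check, but it is not a complete replacement.

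The complete-case analysis is also free of random draws. It gives readers some seed-free comparison, though not necessarily one that uses every observed visit under the same assumption. Finally, any finite m leaves some noise. That is true, but going from 10 to 100 cuts its SD by √10, about 3.2-fold.

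**Conclusion.** The point holds as a minor improvement. The planned inference at m = 10 is valid and about 98-99% efficient. A p-value whose limit is 0.05 could be reported from roughly 0.025-0.03 to 0.08-0.09, and two runs would disagree on significance in about 2-8% of all trials, against about 1-2% with 100 imputations. These figures rest on an assumed FMI of about 0.1-0.2, assumed visit correlations, monotone dropout and a reading of the SD as 0.44 D. The rates from whole-trial simulation are imprecise. If the final p-value is well away from 0.05, the choice of m will not matter to the conclusion.

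**What to change.** In the Statistical Analyses section, replace 10 imputations by 100, or at least 50. The cost is one number in the text and minutes of computing. The estimand, the missing-at-random assumption and the model stay the same, so comparability with the phase 1 study is not harmed.

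Optionally, add to the sensitivity analyses of the primary outcome the same repeated-measures model fitted to all observed visits without imputing outcomes. It makes the same assumption with no random draw, and so gives a stable reference if the imputed result is borderline. State how any child with a missing covariate is handled in it. Few such children are expected for age and baseline refraction, because both are recorded before randomization.
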